#### Data collection timing

Intervention sites will participate in baseline surveys then 8 months of the MATES in Manufacturing program from the first GAT on site, with follow-up surveys administered 8 months after intervention initiation. Wait-list control sites will participate in baseline surveys (month 0) then follow-up surveys 8 months later. At wait-list control sites, the MATES program will commence following the 8 month surveys, then continue for at least 8 months. See Fig. 2: schedule of enrolment, interventions, and assessments.

**Fig. 2 Fig2:**
[figure not shown]
MATES in Manufacturing cluster RCT: schedule of enrolment, interventions, and assessments

### Data collection (2): qualitative implementation evaluation

Volunteers for Connector and ASIST roles at participating sites will be recruited through posters with information provided for contacting the research team (phone numbers and QR codes). Program participants (including those recruited to be Connectors and ASIST workers) and Field Officers will be interviewed in separate focus groups or individual interviews, as is feasible for scheduling. We will aim to conduct focus groups in person, but depending on the state of COVID-19 restrictions at the time, we may conduct individual or focus group interviews by Zoom.

Informed consent will be provided on recruitment and scheduling of interviews. The same safety protocol described for the surveys will be applied in the context of focus group interviews.

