The following Research Questions (RQ) will be addressed using mixed methods for RQ 1–3 and quantitative methods for RQ 4–6:Was the MATES in Manufacturing program implemented as designed?What were the barriers and facilitators to participation in, and implementation of, MATES in Manufacturing?What were participant and staff experiences of the program, including any noted outcomes arising (positive, negative, or other)?Was suicide prevention literacy increased by the MATES in Manufacturing program relative to wait list controls? (process evaluation)Did intentions to seek help increase in the MATES in Manufacturing program relative to wait list controls? (primary outcome)Did help seeking behaviour increase, and levels of distress and suicidal ideation decrease, in the MATES in Manufacturing program relative to wait list controls? (secondary outcomes)

We also aim to evaluate the cost-effectiveness of the intervention if it is shown to have a significant positive effect on the primary outcome of help-seeking intentions.

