**Fig. 1 Fig1:**
[figure not shown]
Schematic representation of MATES in Manufacturing workplace suicide prevention program: General Awareness trained workers (at centre) can access or be referred to Connectors and ASIST workers on site, and on-site supports are complemented and extended by MATES case managers who can further support and refer workers in need to a range of services (illustrative examples of services in outermost ring)

Initially, a one-hour universal General Awareness Training (GAT) is provided for all workers on a site. Volunteers for half-day Living Works’ SafeTalk ‘Connector’ training are recruited during the GAT, and subsequently trained as the persons on site who can ‘connect’ workers in need to appropriate sources of help. Distressed workers can either approach a Connector him- or herself, or a Connector might approach someone based on observation, or concerns expressed by a workmate. ‘Help’ in this context is for mental health or suicidality, or for any issues that could contribute to distress, such as financial stress, alcohol and drug use, or relationship concerns. Volunteers are fundamental to the implementation of the MATES program, and the program aims to have an average of 1 in 20 workers on-site trained as Connectors. In addition to Connector training, MATES also delivers LivingWorks’ Applied Suicide Intervention Skills Training (ASIST): a 2 day session that equips participants with the skills to co-develop a safety plan with an individual at immediate risk of suicide. The program aims to have one to two ASIST-trained workers on each worksite.

Implementation of GAT on site is the starting point of the intervention. For those sites randomly assigned to intervention, the intervention will occur for 8 months during the study period, and then will continue beyond that timepoint at the discretion of the participating sites. Similarly, for sites randomly assigned to the wait-list control condition, the intervention will begin 8 months from the date of baseline assessment, and continue for at least 8 months thereafter. Participants in the trial will have indefinite access to MATES’ help line.

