#### Recruitment of participants within study sites (clusters)

All workers employed at each participating site will be eligible for the MATES program and all will be invited to participate in baseline and follow-up surveys (census sampling). We expect participants to be disproportionately male and blue-collar workers (estimated 75% males in Australian manufacturing sector). There will be two i*nclusion criteria: 1)* Employees or workers in the manufacturing industry who are working at participating sites of the MATES in Manufacturing program, including casual/temporary, contract, and continuing/permanent employees, and 2) Basic English proficiency for program activities (which will be conducted in English); however, surveys and some printed information on the program have also been translated into Vietnamese and Mandarin, and are available on an as-needed basis (some sites include a number of Vietnamese and Chinese workers). There is one e*xclusion criterion:* Individuals aged under 18 years.

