### Measures (2): implementation evaluation

We will monitor and record the number of program activities and participation levels in program activities (e.g., percent of workers on site attending GAT; number and percent of GAT trainees recruited and successfully trained as Connectors). In addition, we will measure suicide prevention literacy as a process/implementation measure using the literacy of suicide scale short form (LOSS). Each of the items on the LOSS is responded to on a 3-point scale (“True”, “False”, or “I don’t know”), with correct responses allocated a score of 1 and incorrect or “I don’t know” responses assigned a score of 0 (e.g., sample item: “People who have thoughts about suicide should not tell others about it”). Total scale scores are calculated by summing item scores, yielding a total literacy score (per cent correct). The LOSS has been validated by using Item Response Theory to identify items that had the strongest discrimination of the underlying literacy construct [24].

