### Analysis (2): implementation evaluation

Descriptive analyses will be reported on frequencies of program intervention activities relative to plans, and participation levels in program activities.

Interview transcripts will be analysed using descriptive thematic analysis [26] to answer the following Research Questions:Was the MATES in Manufacturing program implemented as designed?What were the barriers and facilitators to participation in, and implementation of, MATES in Manufacturing?What were participant and staff experiences of the program, including any noted outcomes arising (positive, negative, or other)?

The suicide prevention literacy process measures collected by survey will be analysed as above for the quantitative effectiveness evaluation, Research Question 4:4)Was suicide prevention literacy increased by the MATES in Manufacturing program relative to wait list controls? (process evaluation)

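### Research Question 2 asks what keeps workers from taking part, but workers who attended no program activity are not among those to be interviewed

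*Protocol article*

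**What the plan says.** The Introduction lists six research questions, which "will be addressed using mixed methods for RQ 1–3 and quantitative methods for RQ 4–6". The second, repeated under Analysis (2): implementation evaluation, reads: "What were the barriers and facilitators to participation in, and implementation of, MATES in Manufacturing". It has two parts, participation and implementation.

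The eligible population is the whole workforce of each site: "All workers employed at each participating site will be eligible for the MATES program".

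Data collection (2): qualitative implementation evaluation names two interview groups: "Program participants (including those recruited to be Connectors and ASIST workers) and Field Officers will be interviewed in separate focus groups or individual interviews". The only recruitment route it gives is in the sentence before: "Volunteers for Connector and ASIST roles at participating sites will be recruited through posters with information provided for contacting the research team".

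On the quantitative side, Measures (2): implementation evaluation says: "We will monitor and record the number of program activities and participation levels in program activities". It adds a suicide literacy score. For Research Questions 1 to 3, Analysis (2) adds descriptive reporting of activity and participation frequencies and then turns to the interviews: "Interview transcripts will be analysed using descriptive thematic analysis".

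**The concern.** A question about barriers to participation is partly a question about people who did not participate. If interviews are open only to those who took part and those who deliver the program, the sample is selected on having got past the barrier under study. Reasons for staying away, such as shift patterns, distrust or discomfort with the topic, would then reach the analysis only through other people. (These examples are mine; the article lists none.)

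The Discussion gives these results real work to do. The combined qualitative and quantitative evidence is meant to explore local factors that could alter implementation and effectiveness. If the effect is null or uneven across sites, low uptake is one of the first explanations a reader will look for, and the plan as written gives no direct account of what caused it.

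**Working it through.** The article gives no figure to reproduce. The check sets the question beside each source that could answer it.

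1. **Who can meet a barrier to participation?** Any worker at a participating site. Recruitment of participants within study sites makes all of them eligible, and the Intervention description says that the general awareness training (GAT) is for everyone on site.

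2. **Who is interviewed?** Program participants and Field Officers. Connectors and ASIST workers are a subset of the first group, because the sentence says that participants include them. A worker who attended GAT and went no further is still a program participant and can be interviewed. A worker who attended nothing is in neither group.

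3. **Does the recruitment sentence widen this?** No. Read literally, it concerns people in, or volunteering for, Connector and ASIST roles. The Intervention description says that Connector volunteers "are recruited during the GAT, and subsequently trained as the persons on site who can" link colleagues to help. The posters are therefore best read as recruiting to interviews and not to the role. On either reading they do not reach non-attenders, and no route is stated for other participants.

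4. **Does the quantitative part fill the gap?** It yields activity counts, attendance percentages, Connector uptake and a literacy score. These show how many did not attend, not why. None of the survey measures described under Measures (1) or Measures (2) asks for reasons for not taking part.

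5. **Does any other channel fill it?** Ethics approvals and monitoring describes Steering Group meetings at which companies, unions and MATES staff raise concerns. The article presents these as trial monitoring and does not assign them to Research Question 2.

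6. **How large is the group?** If *a* is the share of workers at a site who attend at least one activity, the share with no first-hand voice is 1 − *a*. It is zero if everyone attends (*a* = 1) and grows as attendance falls. The article gives no value for *a*. The 74% average under Trial status is participation in the baseline survey, not in the program, and cannot stand in for it. The planned attendance records will show the size once the program has run.

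**The case against.** **The article is condensed.** The qualitative evaluation has its own ethics approval from a second university, and sampling detail, poster wording and interview guides normally sit in a fuller protocol. That is fair as far as it goes. But the article is not silent on who is interviewed: it names the groups, and they do not match the question. If the fuller protocol already admits non-attenders, only the article's wording needs to be aligned.

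**The sample fits the narrower scope.** Evaluation study design confines the qualitative part to implementation barriers and participants' experiences, which these interviewees can cover. This is true, and it offers a fallback. It does not remove the wider wording of Research Question 2 in the Introduction and Analysis (2).

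**Interviewees can say a good deal about participation.** Taking part has levels: GAT, Connector, ASIST. People who stopped at the first can explain why they went no further, and Field Officers visit sites regularly and hear reasons for non-attendance. This stands. What is missing is a first-hand account from those who attended nothing.

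Several stronger readings are tempting, but the documents do not support them:

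- *Non-volunteers are excluded.* They are not, if they attended GAT (step 2).
- *Nearly the whole workforce is left out.* At a 100-worker site, the target of 1 Connector per 20 workers gives 100/20 = 5, plus one or two ASIST workers, so 6 to 7 people. The remaining 93 to 94% are outside those roles, but they are not thereby outside the interview sample.
- *Every interviewee self-refers from a poster.* The poster sentence covers Connector and ASIST volunteers only.
- *Research Question 3 is also mismatched.* It asks about participant and staff experiences, and those are the groups interviewed.
- *Managers and union contacts must be interviewed.* That is a design preference. The article says that survey dates are agreed with the company or site managers and does not give union delegates that role. Both sides already report through the Steering Group.

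**Conclusion.** The point holds in a limited form. Research Question 2 includes barriers to participation, the named interview groups leave out workers who attended no activity, and no other data source described records their reasons. Followed as written, the plan gives only second-hand or survivors' accounts of what kept workers out. It would go too far to say that Research Question 2 cannot be answered: implementation barriers, and barriers at the later levels of participation, are reasonably covered.

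The extent is unknown because program attendance is not given; with full attendance at every site the gap would vanish. Under-representation of such barriers is the likely direction, not a demonstrated result. The conclusion assumes that a program participant means someone who attended at least one activity, which is the natural reading but is not defined. Randomisation, the primary outcome, its analysis and participant safety are not affected. This is an inexpensive improvement to the implementation evaluation.

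**What to change.** In Data collection (2), extend interview eligibility and the recruitment wording to any worker at a site where the program has run, stating expressly that workers who attended no activity are welcome. In Analysis (2), state that barriers to participation will be reported separately for participants, non-participants and Field Officers, so that first-hand and second-hand accounts can be told apart.

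If non-participants cannot be recruited, say so and narrow the Research Question 2 conclusion to implementation barriers and participant experiences, in line with Evaluation study design.

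The cost is revised recruitment wording, an ethics amendment and a few more interviews by the same team. The main drawback is practical: people who avoided the program may also decline an interview, so this group may stay small.

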### Measures (1): effectiveness evaluation

#### Help-seeking sources & intentions (primary outcome)

Help-seeking intentions will be measured using the General Help-seeking Behaviour Questionnaire (GHSQ). GSHQ questions will be modified to present 12 different sources of help seeking (including a MATES worker or Connector and an open-ended option for ‘other’), and participants will be asked to rank their help-seeking intentions prefaced by “if you were feeling overwhelmed and unable to cope.” This phrasing was derived from a qualitative study on how blue-collar male workers conceptualise emotional and suicidal distress, with the results indicating that blue collar male workers are inclined to emphasise a loss of agency [19]. Intentions will be ranked from *extremely unlikely* to *extremely likely on a 7-point scale* [20]. A single summary measure across all the 12 options will be computed by summing the responses (reverse scoring the ‘no one’ option).

#### Help sought (secondary outcome)

Among those who report having felt overwhelmed or unable to cope at any point in the preceding 6 months (yes/no), forms of help sought during the preceding 8 months will be measured using the General Help-seeking Behaviour Questionnaire (GHSQ). GSHQ questions will list the same 12 sources of help as detailed in the primary outcome of help-seeking intentions, except in this case asking whether help has been sought, and how frequently (never/rarely/sometimes/often/always). A single summary measure across all the 12 options will be computed by summing the responses (reverse coding the ‘no one’ option).

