### Analysis (1): quantitative effectiveness evaluation

The primary analysis will be undertaken on an intention-to-treat basis: including all participants as randomised, regardless of treatment received or withdrawal from the study. Mixed-model Repeated Measures (MMRM) analyses will be used because of the ability of this approach to include participants with missing data. Cluster effects will be modelled using a random site effect. An unstructured residual variance-covariance matrix will accommodate within-participant dependency. The statistical significance of the primary outcome will be evaluated in a planned comparison of change from baseline to 8 months post-initiation of intervention in the active arm compared to 8-month change in the waitlist group. Tests of significance will use appropriate degrees of freedom adjustment where necessary (i.e., the Kenward-Roger method based on the observed information matrix). Where necessary, transformation of the outcome variable will be undertaken to ensure distributional assumptions of the model are met.

For binary outcomes (prevalence of suicidal ideation) and other non-continuous outcomes (severity of suicidal thoughts and behaviours), comparable generalized mixed models will be used with population average effects of intervention being compared.

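### Help sought is compared only among workers who report being overwhelmed at follow-up, a comparison that randomisation does not protect, and its 6-month filter conflicts with its 8-month outcome window

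*Protocol article*

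**What the plan says.** All references are to the protocol article.

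- **Help sought (secondary outcome).** Who contributes a score: "Among those who report having felt overwhelmed or unable to cope at any point in the preceding 6 months (yes/no), forms of help sought". The period scored follows in the same sentence: "forms of help sought during the preceding 8 months will be measured". The score sums frequency ratings over 12 sources of help. No score is given for workers who answer no to the filter.
- **Introduction, research question 6.** "Did help seeking behaviour increase, and levels of distress and suicidal ideation decrease, in the MATES in Manufacturing program relative to wait list controls". Help-seeking behaviour and distress are thus both expected to change.
- **Data collection timing.** Intervention sites: "with follow-up surveys administered 8 months after intervention initiation". Control sites: "Wait-list control sites will participate in baseline surveys (month 0) then follow-up surveys 8 months later".
- **Sequence generation, randomisation and allocation concealment.** Blinding is not feasible after baseline. The Trial status section says baseline surveys were completed before assignment.
- **Analysis (1).** The primary analysis is by intention to treat, "including all participants as randomised, regardless of treatment received or withdrawal from the study", using a repeated-measures mixed model. Help sought is not named there.

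**The concern.** The filter asks whether the worker felt overwhelmed or unable to cope. At baseline the answer precedes allocation and does no harm to the randomised comparison. At follow-up it is given by workers who know their arm, about a state the program is meant to change. If distress falls, fewer intervention workers answer yes, and those who do may be more severe cases. If awareness training makes workers readier to say they were struggling, more answer yes, and the added cases may be milder. Either way the two yes groups can differ in make-up when the program has no effect on help-seeking itself.

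Help sought is the effectiveness outcome that measures help actually sought, so it carries the help-seeking part of research question 6. As defined, a positive, null or negative result cannot be separated from a change in who answers yes. The baseline and follow-up filters may also select different workers, which weakens a comparison of change from baseline.

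The two recall periods in one sentence are a separate conflict over what the outcome covers.

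**Working it through.** **1. Timing of the filter.** Follow-up is at month 8. The preceding 6 months are months 2 to 8, counted from program start (intervention) or baseline (control). The answer itself is given after allocation in both arms.

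**2. Window conflict.** 8 − 6 = 2 months. A worker overwhelmed and helped only 7 to 8 months before the survey, that is in the first two months after program start, answers no and is excluded, although that help lies inside the outcome window. A worker overwhelmed only in the last two months before the survey passes the filter.

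**3. The plan's own sample-size figures** (Power and sample size: d = 0.30, ICC = 0.02, alpha 0.05 taken as two-sided, 80% power). These are for the primary outcome; none is given for help sought.

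- Per arm, unclustered: 2 × ((1.96 + 0.84)/0.30)² = 174.4 (computed with unrounded normal quantiles).
- Sites = 2 × 174.4 × [1 + (m − 1) × 0.02] / m.
- m = 30: 18.4 (stated 19). m = 50: 13.8 (stated 14). m = 100: 10.4 (stated 10, power 78.5%).

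The figures reproduce apart from rounding to whole sites, and the point does not depend on them.

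**4. Illustrative size of a spurious difference.** The documents give no share of workers overwhelmed, no shift in it, and no relation between severity and help sought. All three are assumed here, with no effect on help-seeking.

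*Simple mix:* 30% of controls pass the filter, and milder cases score 0.5 SD lower.

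- Program adds 5 points of mild cases: (30μ + 5(μ − 0.5))/35 = μ − 2.5/35, a shift of −0.071 SD.
- Program removes 5 points of cases scoring 0.5 SD below the remaining 25: shift = 0.5 × 5/30 = +0.083 SD.

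*Threshold model (simulation):* severity is normal, the worker answers yes above a cut-off, and severity correlates 0.2 to 0.4 with the help score. The control yes rate is 30%.

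| Yes rate, intervention | Spurious difference (SD) |
|---|---|
| 20% | +0.05 to +0.10 |
| 25% | +0.02 to +0.05 |
| 30% | 0 |
| 35% | −0.02 to −0.04 |
| 40% | −0.04 to −0.08 |

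**5. Scale against sampling error.** With 30% of 1000 workers there are 300 in the subset, 30 per site at 10 sites. Design effect = 1 + 29 × 0.02 = 1.58. Standard error = √(2 × 1.58/150) = 0.145 SD. A shift of 0.071 to 0.083 SD is 0.49 to 0.57 standard errors. By normal approximation it raises a 5% two-sided error rate to roughly 8 to 9%.

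**6. Information in the subset.** Power for d = 0.30, if 10/20/30/40/50% answer yes, is 28/44/54/61/66%, against 78.5% in all 1000. The 0.30 is the primary outcome's target, used only as a yardstick.

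**The case against.** The strongest reply has five parts.

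- **The arms may be perfectly comparable.** A reader might infer that the filter makes the arms non-comparable. The documents do not support that. With equal yes rates and equal case mix the bias is zero, and nothing shows that either will differ. What stands is that randomisation no longer guarantees it.
- **The window conflict is common to both arms.** A reader might treat it as a source of bias between arms. It is mainly a conflict of definition, possibly a drafting slip, since the suicidal ideation item and the health service questionnaire also use 6 months. It would become differential only if the program prompted early help followed by recovery.
- **Handling of no answers is not stated.** A reader might infer that the mixed model treats them as missing at random and so extrapolates help-seeking to workers without need. The article does not say so. It names intention to treat for the primary analysis and does not mention help sought there. An analysis plan may settle the scoring. But the restriction to yes responders is fixed in the outcome definition, and nothing in Analysis (1) repairs it.
- **Help sought is not the only record of behaviour.** Mental-health service use is also collected at 8 months, with no such filter mentioned. This is right, although that measure serves the economic evaluation.
- **The assumed bias is modest**, about half a standard error. This also stands and is a reason not to overstate the point. The primary outcome asks a hypothetical question of everyone and is unaffected.

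**Conclusion.** The point holds for a secondary outcome. The between-arm comparison of help sought among workers who report being overwhelmed at follow-up is not protected by randomisation and may be biased in either direction. Size and direction cannot be computed from the documents. The range of 0.02 to 0.10 SD in the working rests wholly on an assumed 30% yes rate in controls, assumed shifts of 5 to 10 percentage points, and an assumed link between severity and help sought.

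The 6-month and 8-month periods contradict each other within one sentence and must be reconciled. That is a definition error affecting both arms, not evidence of bias between them.

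**What to change.** 1. For research question 6, define a help-seeking outcome for all follow-up respondents as randomised, from items already collected. For example, use three categories: overwhelmed and sought help; overwhelmed and sought no help; not overwhelmed. The generalised mixed models already planned for non-continuous outcomes can be used.
2. Report the proportion overwhelmed by arm beside it, so that a change in distress or disclosure can be told apart from a change in help-seeking. This matters because the categories contain the filter answer. If 40% of overwhelmed workers seek no help (assumed), a yes rate of 30% gives 0.40 × 30 = 12% in the second category, 35% gives 14%, and 25% gives 10%, with no change in help-seeking.
3. Keep the frequency sum among overwhelmed workers, labelled descriptive and not protected by randomisation.
4. State one recall window for filter and outcome, the same in both arms, and note any difference from the baseline form already used.

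Cost: items 1 to 3 need only analysis wording. Item 4 may mean editing the follow-up form, including its Vietnamese and Mandarin versions. Baseline is complete at 8 sites, so a changed window could make the two waves differ. The categorical outcome carries less detail than the frequency sum and partly reflects distress and disclosure. A measure of any help sought in everyone is possible only if workers who answered no also completed the help items.

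### Reversing the 'no one' row on a past-frequency scale makes the help-sought score ambiguous for workers who sought no help

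*Protocol article*

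**What the plan says.** Under Help sought (secondary outcome), the protocol article reuses the item list of the primary outcome: "GSHQ questions will list the same 12 sources of help as detailed in the primary outcome of help-seeking intentions". The response scale changes, however. Workers answer a question "asking whether help has been sought, and how frequently (never/rarely/sometimes/often/always"). The scoring rule is then that one total over all 12 options "will be computed by summing the responses (reverse coding the ‘no one’ option").

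The same rule appears under Help-seeking sources & intentions (primary outcome), "A single summary measure across all the 12 options will be computed by summing the responses (reverse scoring the ‘no one’ option"), but there the responses are on a 7-point likelihood scale.

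The help-sought items are analysed only "Among those who report having felt overwhelmed or unable to cope at any point in the preceding 6 months (yes/no"). The score serves the behaviour part of the sixth research question in the Introduction ("Did help seeking behaviour increase, and levels of distress and suicidal ideation decrease"), so a higher score counts as benefit.

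The article gives no numeric codes for the five frequency levels, no wording for the 'no one' row, and no rule for a worker who ticks 'never' on every row.

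**The concern.** Reversal suits the intentions scale: rating 'no one' as extremely unlikely is a coherent answer in favour of seeking help. On a scale of past frequency, 'never' against 'no one' has two readings. One worker means that they never went without help. Another sought nothing and is adding one more 'never' to a column of them. Reversal gives both the top mark on that row.

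The row also carries no behaviour of its own, because having gone to nobody is already recorded by 'never' on the 11 source rows. At stake is whether a rise in the score can be read as a rise in help sought, in an outcome that only part of the sample answers.

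**Working it through.** **Inputs.** There are 12 rows, all summed. The rule treats 'no one' as one of them, which leaves 11 source rows. There are five ordered frequency levels. The codes are not stated, so 0-4 and 1-5 are both assumed. The article gives no score for this measure, so there is no figure to reproduce.

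**Formula.** Count 'never' as 0 and 'always' as 4. Let S be a worker's total over the 11 sources and m the level ticked on 'no one'.

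- Codes 0-4: score = S + (4 − m), range 0 to 48.
- Codes 1-5: score = (S + 11) + (5 − m) = S + 16 − m, range 12 to 60. This is always 12 more than the first, so the ordering is the same.

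**Scores.**

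| Worker | S | m | 0-4 codes | 1-5 codes |
|---|---|---|---|---|
| No help; 'no one' never | 0 | 0 | 4 | 16 |
| No help; 'no one' always | 0 | 4 | 0 | 12 |
| One source rarely; 'no one' never | 1 | 0 | 5 | 17 |
| One source rarely; 'no one' rarely | 1 | 1 | 4 | 16 |
| One source sometimes; 'no one' sometimes | 2 | 2 | 4 | 16 |
| One source rarely; 'no one' sometimes | 1 | 2 | 3 | 15 |
| One source sometimes; 'no one' often | 2 | 3 | 3 | 15 |

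The first two workers did the same thing and differ by 4 points. That is as much as a worker gains by moving from 'never' to 'always' on one source.

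**When a non-seeker is not below a seeker.** The all-'never' worker scores 4. This is at least the seeker's score when 4 ≥ S + 4 − m, that is, when S ≤ m. It is a tie if S = m and an inversion if S < m. Since m is at most 4, neither can happen once S is 5 or more. With m = 0 neither can happen for any seeker, because S is at least 1.

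**One-source seekers.** There are 4 source levels × 5 'no one' levels = 20 patterns. S = m in 4. S < m in 3 + 2 + 1 = 6. The seeker is higher in the other 10. This counts patterns and does not estimate how often each occurs.

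**Change within a worker who starts to seek help (0-4 codes).**

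- 'Never' on 'no one' at both surveys: 4 becomes S + 4, a rise.
- Row read literally at both surveys: 0 becomes S + 4 − m, which is at least 1, a rise.
- Reading switches, for example all 'never' and then one source rarely with 'no one' sometimes: 4 becomes 3, a fall.

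**Noise and direction, by assumption.** Suppose a share p of non-seekers tick 'never' on 'no one' and the rest tick 'always'. The spurious SD among non-seekers is 4√(p(1 − p)): 1.7 points at p = 0.25 or 0.75, 2.0 at p = 0.5, and 0.9 at p = 0.05. The row changes the mean gap between seekers and non-seekers by (4 − mean m) − 4p. It shrinks the gap only if mean m exceeds 4(1 − p), which is 3, 2 or 1 at p = 0.25, 0.5 or 0.75. Neither p nor mean m can be taken from the article.

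**After dropping the row.** The score is S. Every non-seeker has 0 (11 on 1-5 codes) and every seeker at least 1 (12), so ties and inversions cannot occur.

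**The case against.** The strongest reply is that the fault depends on wording that the article does not show. If the row reads as a statement that the worker went to nobody, the consistent answer from a non-seeker is 'always'. That scores the minimum, and the reversal works as intended. Item wording and the handling of inconsistent answers are details that a condensed article may leave elsewhere. This stands as a limit on size: no frequency of ties or inversions can be claimed. It does not remove the point, because the summing rule is stated outright, and under it the score of an all-'never' response is fixed at 4 above the minimum.

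A second reply is that surveys are linked within person and the planned comparison, stated for the primary outcome, is of change from baseline, so a stable reading habit largely cancels. The working bears this out for workers who read the row the same way twice. Cancellation is only partial, however. The items count only for workers who report recent difficulty coping, so many may contribute one survey only, and the planned mixed model keeps participants with missing data.

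A third reply is that keeping the row preserves the match with the intentions score. That is a real but small advantage.

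A reader might infer that non-seekers generally score as high as seekers, or that the rule reverses the treatment effect. The documents support neither. The first fails whenever S exceeds m. The second would need workers to switch readings between surveys, in numbers and in a pattern by arm for which there is no evidence.

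**Conclusion.** The point holds in a limited form. As written, the rule gives two scores, 4 points apart, to the same absence of help-seeking. It lets an all-'never' worker tie with or outscore a seeker whose source total is no more than their 'no one' answer. This follows from the stated rule under either coding, given that 'no one' is one of the 12 summed rows. How often it happens rests on row wording and response habits that are not shown. The expected consequence is extra noise and possible attenuation in one secondary outcome. The direction of any shift in the seeker versus non-seeker gap is itself unknown. The primary outcome is not affected, since on its likelihood scale the reversed row has a coherent meaning. Severity is minor.

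**What to change.** Replace the scoring sentence under Help sought with one to this effect: *the help-sought score is the sum of the frequency responses to the 11 help sources, including 'other'; the 'no one' row is not scored and serves only as a consistency check.* State the numeric codes in the same place. The intentions score can stay as it is.

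The cost is one sentence. The survey does not change, and baseline forms already collected can be scored under the new rule. No information about help sought is lost, because 'never' on all 11 sources already identifies a worker who went to nobody. The one small downside is that the item set no longer matches the intentions score exactly. The change should be recorded before outcome data are analysed.
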